### Study design

This study is a prospective, investigator-initiated, multicenter, open-label, randomized controlled study with two experimental therapy groups. We have followed the Standard Protocol Items: Recommendations for Interventional Trials (SPIRIT) 2013 Statement which defines standard protocol items for clinical trials [24] (see Additional file 1). The study algorithm is depicted in Fig. 1 and the SPIRIT and study schedule are given in Figs. 2 and 3. After enrollment, clinical follow-up will be performed 2 days after treatment with 3% hypertonic saline.

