### Physician’s practical treatment guidelines according to the sNa level

The principal purpose of this study will be to compare the rapid intermittent correction group to the slow continuous correction group [29]. According to a review of the medical literature on the treatment of hyponatremia, treatment with hypertonic (3%) saline is recommended in cases of severe symptomatic hyponatremia [1, 15, 16]. Therefore, the rate of infusion of 3% saline will be stratified based on the symptom severity in each group. After randomization, the participants will undergo either rapid intermittent correction or slow continuous correction of hyponatremia for 48 h. Treatment in the intermittent bolus group will comply with European guidelines published in 2014, and the slow continuous infusion will be guided by widely accepted methods [1, 13–16]. The treatment goals are to raise the sNa level by 5–9 mmol/L from the initial sNa and to achieve symptom relief within the first 24 h, and to raise the sNa level by 10–17 mmol/L from the initial sNa or ≤130 mmol/L, and to achieve symptom relief during the 48 h [10–12]. We will also check for overcorrection at every sample time point and conduct relowering treatment. Relowering treatment is performed as below if the achieved sNa level is ≥10 mmol/L at any sample time point within the first 24 h or the achieved sNa level is ≥18 mmol/L at any sample time point within 48 h [1, 13–16]. The treatment goal, relowering treatment strategy, and cause-specific treatment of hyponatremia will be applied to each group equally.

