### Safety issues

All adverse events related to overcorrection will be recorded and followed up during the study period or until resolution during treatment with 3% hypertonic saline. Any serious adverse events will be reported to investigators and the Ethics Committee. We will check for overcorrection at every sample time point and conduct relowering treatment as needed. Relowering treatment is performed as follows if the achieved sNa level is ≥10 mmol/L at any sample time point within the first 24 h or if the achieved sNa level is ≥18 mmol/L at any sample time point within 48 h: discontinuing ongoing active treatment; initiating infusion of 10 mL/kg of 5% dextrose over 1 h; and/or adding desmopressin 2 mcg [1].

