### Sample size calculation

In the medical literature, ODS is a critically important outcome, but the incidence of ODS is very low [1, 15, 31]. Therefore, as a surrogate marker of ODS, the rate of overcorrection >12 mmol/L within 24 h or >18 mmol/L within 48 h was calculated for the primary study outcome. A previous study reported that the overcorrection rate was 10–16% with slow continuous correction of hyponatremia [10]. However, there was insufficient information for estimating the rate of overcorrection with intermittent bolus infusion. Based on clinical practice and experience, we estimated that the overcorrection rate was 32% with slow continuous correction during a recent 1-year period. We therefore expect that the rate of overcorrection will be 5% in patients treated with rapid intermittent correction and the rate of overcorrection with slow continuous correction could be as high as 20%. We calculated the required sample size for an estimated dropout rate of 15%, a two-sided level of significance of *α* = 5%, a power of 80%, and found that 89 participants will be required in each group to find a significant difference using a *χ*
^*2*^ test. A total of 178 participants will be included in the analysis. We have considered one interim analysis at the time that a half of subjects complete the study. The O’Brien-Fleming’s alpha spending function will be used to test the first interim and final analysis of primary outcome.

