### Statistical analyses

Statistical analyses will be performed on both per-protocol (PP) and intention-to treat (ITT) bases. For the PP analysis, all participants who completed the study will be included to evaluate the primary and secondary outcomes. For the ITT analysis, all participants who were enrolled and randomized to one of the two groups will be included. The baseline characteristics and laboratory data will be presented as means and standard deviations for continuous variables and as frequencies and percentages for categorical variables.

The incidence of overcorrection, ODS, relowering treatment, and target correction rate (achieved sNa <10 mmol/L within the first 24 h and sNa <18 mmol/L within 48 h) will be compared between the two groups using a *χ*
^*2*^ test and Fisher’s exact test. In interim analysis, if the *P* value < 0.003 then we would stop the study early for significance of outcome. If not, we would recruit another half of subjects. The differences in changes in symptoms and GCS scores between pretreatment and 24 and 48 h, time to reach target sNa, time to achieved sNa ≥5 mmol/L for the first time, and length of hospital stay will be analyzed using Student’s *t* test or the Mann-Whitney *U* test. A value of *P* < 0.05 will be considered statistically significant. All analyses will be performed using SPSS Statistics software V21.0 (IBM Corporation, Armonk, NY, USA).

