We will also include the participants with chronic hyponatremia. It is well-known that using a threshold of 48 h is frequently applied to distinguish “acute” from “chronic” hyponatremia [1]. Because not all patients have sNa measured within 48 h prior to visiting the emergency room. Therefore, it is practically impossible to exclude the patients with chronic hyponatremia based on these definitions. Second, the most important factor in determining treatment of hyponatremia is the presence of symptoms, irrespective of biochemical degree or timing (acute versus chronic) of hyponatremia [1]. We will enroll the patients with moderately severe to severe symptoms who need to be treated. In other words, even if the patients belong to the chronic hyponatremia group, the patients with symptomatic hyponatremia need to be treated. Therefore, we thought that including the patients with chronic hyponatremia is reasonable and inevitable.

We will use the overcorrection rate as a primary outcome. ODS is a serious complication, which should be prevented for patient safety, and it is one of the critical outcomes in the management of hyponatremia, but it is difficult to diagnose and very uncommon [1, 31]. Several studies have reported that the rate of overcorrection is strongly correlated with ODS, and is highly sensitive for predicting ODS. In terms of safety issues, the overcorrection rate might be a good laboratory outcome in our trial [1, 15, 32, 33].

This trial may have some limitations. We will enroll patients who visit the emergency room in general hospitals; therefore, patients with hospital-acquired hyponatremia will be excluded. Second, various situations may affect protocol violations, considering that on-duty physicians and nurses may work in shifts. For this, reason we made both protocols as simple as possible.

In summary, the SALSA study is the first prospective, multicenter, randomized, open-label, controlled clinical trial to evaluate the clinical usefulness of rapid intermittent correction management in patients with moderately severe or severe hyponatremia. The aim of this study is to evaluate the efficacy and safety of rapid bolus correction compared with slow continuous correction of hyponatremia.

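### The per-protocol set is defined by completing the study and not by adherence, so it is a completers set and cannot show the effect under the assigned regimen

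*Protocol article*

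**What the plan says.** Under Statistical analyses the article plans two analysis sets: "Statistical analyses will be performed on both per-protocol (PP) and intention-to treat (ITT) bases". The first is defined by "For the PP analysis, all participants who completed the study will be included to evaluate the primary and secondary outcomes", the second by "For the ITT analysis, all participants who were enrolled and randomized to one of the two groups will be included". Neither is named as primary. The article nowhere adds an adherence criterion or a list of major deviations, and it does not define completion.

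Four other places bear on this:

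- **Treatment period and follow-up.** The treatment guidelines section says that "the participants will undergo either rapid intermittent correction or slow continuous correction of hyponatremia for 48 h". Study design says that "clinical follow-up will be performed 2 days after treatment with 3% hypertonic saline". I therefore take completion to mean remaining in the study to 48 h.
- **Expected violations.** The Discussion lists as a limitation that "various situations may affect protocol violations, considering that on-duty physicians and nurses may work in shifts".
- **Expected loss.** The Sample size calculation allows for an "estimated dropout rate of 15" per cent.
- **Relowering.** Under Safety issues, relowering treatment begins with "discontinuing ongoing active treatment".

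**The concern.** A per-protocol analysis is meant to ask what happens when patients receive the regimen they were assigned. The rule here selects on something else.

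- **It keeps violators.** Patients given a rate or volume other than the one laid down, or treated by the other method, remain in the set if they reach 48 h. In an open-label trial with several treatment decisions over two days, these are the patients whom a per-protocol set exists to handle.
- **It drops early leavers regardless of adherence.** The primary outcome can be met within the first 24 h, so a patient may have the event, leave before 48 h and be removed.

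The two mechanisms mislead in different ways. Retained violators affect ITT and this set alike, so the two would agree and a reader would wrongly conclude that violations did not matter. Selective exit would make the two differ, and a reader would wrongly put the difference down to adherence. As the article uses both sets for the primary and secondary outcomes and does not rank them, either misreading could affect the main conclusion.

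**Working it through.** **Inputs from the Sample size calculation:** overcorrection 20% (slow continuous) and 5% (rapid intermittent), two-sided alpha 5%, power 80%, dropout 15%, 89 per group, 178 in total.

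**The plan's own figure.** With pooled variance under the null and no continuity correction, the mean rate is 0.125 and

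n = [1.96 × √(2 × 0.125 × 0.875) + 0.8416 × √(0.20 × 0.80 + 0.05 × 0.95)]² / 0.15² = 75.1, so 76 per group.

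Allowing for dropout, 75.1/0.85 = 88.4, which rounds up to the stated 89. Starting from the rounded 76 gives 90 by division and 88 by multiplying by 1.15. The stated figure reproduces, and nothing in this point changes it.

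**Size of the completers set.** 89 × 0.85 = 75.65, about 76 per group. 178 × 0.15 = 26.7, so about 27 patients would be excluded.

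The article gives no violation rate and no reasons for dropout. The fractions in (a) and (b) are assumptions that show a range. Power is for 76 per group with the same formula.

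**(a) Retained violators.** Let a share v of completers in each arm in effect receive the other regimen and take on its event rate. The slow-arm rate is 0.20(1 − v) + 0.05v, and the rapid-arm rate is 0.05(1 − v) + 0.20v.

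| v | Slow | Rapid | Difference | Power |
|---|---|---|---|---|
| 0 | 20.0% | 5.0% | 15 points | 80% |
| 10% | 18.5% | 6.5% | 12 points | 61% |
| 20% | 17.0% | 8.0% | 9 points | 39% |

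The completion rule removes none of this dilution.

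**(b) Selective exit.** Let overcorrected slow-arm patients leave r times as often as other slow-arm patients, with 15% leaving overall. The others leave at q = 0.15/(0.80 + 0.20r), and the slow-arm rate among completers is 0.20(1 − rq)/0.85. The rapid arm is held at 5%.

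| r | q | rq | Slow rate among completers | Difference | Power |
|---|---|---|---|---|---|
| 1 | 15.0% | 15.0% | 20.0% | 15.0 points | 80% |
| 2 | 12.5% | 25.0% | 17.6% | 12.6 points | 70% |
| 3 | 10.7% | 32.1% | 16.0% | 11.0 points | 60% |

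**The case against.** **The definition may be completed elsewhere.** Lists of major violations are commonly left to the full protocol or SAP, and neither is shown. That would answer a complaint about missing detail. Here the article states a rule, and it admits everyone who completes. Followed as written, the rule leaves no room to exclude a violator.

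**ITT is planned and both protocols were kept simple.** Both are true. The Discussion says the protocols were simplified because violations were expected. ITT on all randomised patients preserves the randomised comparison, and this limits the harm. It does not make the second set informative about adherence.

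**A stronger reading is that relowered patients count as non-completers**, so that the patients with the fastest sodium rise are removed. The article does not support this:

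- The rule refers to completing the study, not the infusion.
- Stopping hypertonic saline is routine in both arms once the target and symptom relief are reached.
- Relowering applies to both groups equally, and its incidence is a secondary outcome to be evaluated in this same set.
- Nothing says that relowering ends participation.

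**A much larger effect might also be inferred.** If half of the overcorrected patients were lost and nobody else, the rates would be 0.10/0.90 = 11.1% and 0.025/0.975 = 2.6%, a difference of 8.5 points. That calculation lets only overcorrected patients leave and does not use the 15% dropout. With 15% leaving the slow arm overall, losing half of the overcorrected would mean that only (0.15 − 0.10)/0.80 = 6.25% of the others leave, an eightfold ratio. Nothing in the article suggests this.

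**Adherence cannot be judged blind to sodium.** This stands in part. The stop and restart rules are functions of the sodium series, so the fluid record alone cannot show whether they were followed. The fix has to allow for it.

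**Conclusion.** The point holds as a defect in a stated definition. The set labelled per-protocol is a completers set: it retains the violations that the article expects and removes early leavers without regard to what they received. This follows from the wording and needs no numerical assumption.

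The size is not known. Under the assumed ranges, the planned 15-point difference would be 12 or 9 points with 10% or 20% of each arm in effect crossed over. It would be about 12.6 or 11.0 points if overcorrected slow-arm patients left two or three times as often as others. Both illustrations shrink the difference, but the article gives no reason to expect any particular exit pattern, and a link between exit and outcome is only a possibility. No stated sample-size figure changes.

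**What to change.** In Statistical analyses:

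1. Name ITT, all randomised patients, as the primary basis and the per-protocol analysis as supportive.
2. Define the per-protocol set by pre-specified major deviations from eligibility and from the assigned regimen: the assigned method, and volumes or rates as the protocol lays them down. Take these from the 48 h fluid records already collected (Clinical and laboratory evaluations).
3. Classify deviations by fixed criteria, without sight of any comparison between arms, before the outcome analysis. Full blinding to sodium is not attainable where an instruction depends on the sodium reading, so fixed criteria are what protects the classification.
4. State that protocol-directed stopping and relowering count as adherence.
5. State that early exit alone excludes no one, with or without an event. Keeping early leavers only if they had the event would bias the rates upward. For example, if 15% of event-free patients left and were excluded, 20% would become 0.20/(0.20 + 0.80 × 0.85) = 22.7%, and 5% would become 0.05/(0.05 + 0.95 × 0.85) = 5.8%.
6. If the present set is kept, label it completers and do not present it as evidence on adherence.

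The cost is a change of wording, some extra record review, and probably a somewhat smaller per-protocol set. By how much cannot be said, because the article gives no violation rate. No treatment rule and no sample-size figure changes.

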### Study participants and measurements

All participants will be selected from among patients visiting the emergency rooms of two general hospitals in Korea (Seoul National University Bundang Hospital, Seoul National University Boramae Medical Center). Patients aged over 18 years who have moderately severe to severe symptoms and glucose-corrected sNa [25] ≤125 mmol/L on the first blood test will be screened for study participation. Moderate symptoms include nausea, headache, drowsiness, general weakness, and malaise [1, 26, 27]. Severe symptoms include vomiting, stupor, seizure, and coma (Glasgow Coma Scale (GCS)).

The following assessments will be performed during the initial emergency room encounter: (1) completion of questionnaire on medical and drug history including the use of antihypertensive medication, diuretics, nonsteroidal anti-inflammatory drugs, selective serotonin reuptake inhibitors, antiepileptic drugs, steroids, and synthyroid, (2) physical examination of all body systems, (3) measurement of height and weight, (4) blood pressure and pulse rate measurement, and (5) assessment of psychological status. Participants, who meet all of the inclusion criteria, do not require exclusion on the basis of the exclusion criteria, and provide written informed consent will be eligible for this study (Table 1).

**Table 1 Tab1:** Inclusion and exclusion criteria

Inclusion criteria	Exclusion criteria
18 years and older	Pseudo-hyponatremia (serum osmolality >275 mOsm/kg)
	Primary polydipsia (urine osmolality ≤100 mOsm/kg)
	Glucose-corrected serum sodium >125 mmol/L
	Initial arterial hypotension (SBP <90 mmHg and MAP <70 mmHg)
Glucose-corrected serum sodium ≤125 mmol/L	Anuria or urinary outlet obstruction
	Decompensated LC (LC with ascites or diuretics use or history of hepatic encephalopathy and varices)
	Bilirubin >2 mg/dL, transaminase levels >2.5 times the upper limit of normal)
Symptomatic patients	Uncontrolled diabetes mellitus (HbA1C >9%)
Moderately severe:	Women who are pregnant or breastfeeding
nausea without vomiting, drowsiness, headache, general weakness, malaise	Within the 3 months prior to randomization, history of cardiac surgery excluding PCA, acute myocardial infarction, sustained ventricular tachycardia, ventricular fibrillation, acute coronary syndrome, cerebrovascular trauma, and increased intracranial pressure
Severe:	
vomiting, stupor, seizures, coma (GCS ≤8)	

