### Randomization

A research coordinator will perform the randomization. A list of random numbers will be generated by an independent statistician. Eligible participants will be randomly assigned 1:1 to either the slow continuous correction group or the rapid intermittent correction group in accordance with the predefined randomization list with a block size of 2. Randomization will be stratified based on the symptom severity related to hyponatremia (moderately severe or severe).

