### Outcome measures

The primary outcome is the incidence of overcorrection, a surrogate marker of ODS, at any given period, defined as follows: increase in sNa level by >12 mmol/L within the first 24 h or increase in sNa level by >18 mmol/L within 48 h. The secondary outcomes will include efficacy and safety; changes in symptoms between pretreatment and 24 and 48 h after treatment with 3% hypertonic saline; time from treatment initiation to an increase in sNa ≥5 mmol/L; time from treatment initiation to the achievement of a sNa >130 mmol/L; incidence of target correction rate, defined as an achieved sNa <10 mmol/L within 24 h and a sNa <18 mmol/L within 48 h; length of hospital stay; incidence of additional treatment; incidence of ODS confirmed by the *International Classification of Disease, 10th Revision (ICD-10)* code or magnetic resonance imaging (MRI); incidence of relowering treatment; and change in GCS score between pretreatment and 24 and 48 h after 3% hypertonic saline treatment.

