### Clinical and laboratory evaluations

The physical examination, laboratory evaluations, and medication reviews will be conducted before treatment; the laboratory evaluations will include a complete blood count, serum electrolytes, blood urea nitrogen, creatinine, calcium, phosphorous, protein, albumin, and glucose; a liver function test; a thyroid function test (TFT); rapid adrenocorticotropic hormone (ACTH) test (basal cortisol, ACTH, cortisol at 30 min and 60 min), serum osmolality; urinalysis, urine electrolytes, urine osmolality. sNa levels will be measured every 6 h for 2 days [30]. The GCS score will be assessed before treatment and at 24 and 48 h of treatment. All types and volumes of administered fluid during 48 h will be monitored.

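### GCS change is tested without adjusting for the baseline GCS that is collected: a valid test, but an inefficient one, with low power if most patients recover to near 15

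*Protocol article*

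**What the plan says.** Outcome measures lists among the secondary outcomes the "change in GCS score between pretreatment and 24 and 48 h after 3% hypertonic saline treatment". Clinical and laboratory evaluations fixes the measurements: "The GCS score will be assessed before treatment and at 24 and 48 h of treatment". A pretreatment value is therefore planned for every patient.

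Statistical analyses then names the quantity and the test. "The differences in changes in symptoms and GCS scores between pretreatment and 24 and 48 h" (with several other outcomes) "will be analyzed using Student’s" t test or the Mann-Whitney U test. Neither baseline GCS nor the severity stratum enters the comparison.

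Two other places matter. Randomization states: "Randomization will be stratified based on the symptom severity related to hyponatremia". Table 1, under Study participants and measurements, defines the two strata. The moderately severe one is "nausea without vomiting, drowsiness, headache, general weakness, malaise"; the severe one is "vomiting, stupor, seizures, coma (GCS ≤8".

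**The concern.** A raw change score uses the baseline with a fixed weight of one. That is efficient only if follow-up GCS rises one point for each point of baseline GCS. A capped scale works against this: a patient who starts at 15 cannot gain, whereas a patient in coma at 8 or below can gain 7 points or more.

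Table 1 makes a wide baseline spread likely. Nausea, headache, weakness or malaise are compatible with a GCS of 15. The severe stratum alone runs from vomiting, which is also compatible with 15, down to coma. Both arms are treated with symptom relief as a goal (Physician's practical treatment guidelines). If that goal is largely met, follow-up scores bunch near 15 and change mostly restates where the patient began.

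At stake is the interpretation of a secondary efficacy result. A non-significant GCS comparison might be read as similar neurological recovery when the test had little chance of showing a difference.

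**Working it through.** **1. The plan's own figure.** The article gives no mean, SD, expected effect or power for GCS, so there is no GCS figure to reproduce. Its one sample size, for overcorrection (20% against 5%, two-sided 5%, 80% power, 15% dropout), reproduces:

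n = [1.96·√(2·0.125·0.875) + 0.84·√(0.20·0.80 + 0.05·0.95)]² / 0.15² = 75.12 per arm; 75.12/0.85 = 88.4, rounded up to 89.

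After dropout, 89 × 0.85 = 75.65, so about 76 per arm. The GCS calculations below use 76 to 89.

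**2. Algebra.** Let s_b and s_p be the SDs of baseline and follow-up GCS, and r their correlation within arm.

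- Var(change) = s_b² + s_p² − 2·r·s_b·s_p
- Residual variance with baseline as covariate = s_p²(1 − r²)
- Difference = (s_b − r·s_p)², which is never negative and is zero only when the slope of follow-up on baseline, r·s_p/s_b, equals 1
- Share of the variance of change that is baseline variance = (s_b − r·s_p)² / Var(change)

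For an effect that the adjusted analysis detects with 80% power, the power of the test on change is Φ(2.80/√ratio − 1.96), where ratio = Var(change)/adjusted variance. With r = 0.4 and assumed SDs:

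| s_b | s_p | Var(change) | Adjusted variance | Ratio | Baseline share | Power of test on change |
|---|---|---|---|---|---|---|
| 2 | 0.5 | 3.45 | 0.21 | 16.4 | 94% | 10% |
| 2 | 1 | 3.40 | 0.84 | 4.05 | 75% | 28% |
| 1 | 1 | 1.20 | 0.84 | 1.43 | 30% | 65% |
| 1 | 2 | 3.40 | 3.36 | 1.01 | 1% | 80% |

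First row: 4 + 0.25 − 0.80 = 3.45; 0.25 × 0.84 = 0.21; (2 − 0.2)²/3.45 = 0.94; Φ(2.80/4.05 − 1.96) = Φ(−1.27) = 0.10.

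The loss is therefore severe when follow-up scores are much less spread than baseline scores, and negligible when they are more spread.

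**3. Simulation with the cap at 15.** Every GCS distribution here is an assumption. Adjusted means ANCOVA on baseline GCS.

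First model, 76 to 89 per arm, robust (HC3) standard errors for the adjusted analysis:

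| Scenario | t on change | Adjusted |
|---|---|---|
| 60% vs 80% of lost points regained | 9–22% | 22–67% |
| Poor recovery | 24–68% | 31–81% |
| 10% of patients worsen | 7–18% | 10–28% |

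In the 60% vs 80% scenario, Mann-Whitney on change had 5–15% power. With no true difference, all tests rejected in about 5% of runs.

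Second model, 76 per arm, severity split held equal between arms, 25–50% severe:

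| Scenario | t on change | Adjusted |
|---|---|---|
| Full return to 15 in 60% vs 90% | 6–12% | 50–80% |
| Full return to 15 in 75% vs 95% | 2–6% | 37–64% |
| 10% vs 30% of deficit regained, none worsen | 49–97% | 76–100% |
| Same, 10% worsen | 19–67% | 22–75% |

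Mann-Whitney on change had 11–16% power in the first of these rows and 6% in the second. Baseline explained 75–94% of the variance of change when 40–95% of patients returned fully to 15, 39–58% when only 10–40% of the deficit was regained, and 15–31% when 10% of patients also worsened. With no true difference, the tests on change rejected in 0.7–3.1% of runs. Rates below 5% are expected when arms are balanced on severity and the analysis ignores it.

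**The case against.** The strongest case is that this concerns efficiency alone, for a secondary outcome with no power claim, and that an unseen analysis plan could add an adjusted analysis. Testing change scores is common and valid. Most of this stands and sets the limits of the point. It does not remove it, because the article itself names the test and the inputs for a better one are already collected.

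Three stronger readings are tempting and are not supported.

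- **That the planned test mainly compares chance baseline differences and has little power, whatever happens.** This needs recovery to near 15 in most patients. The article states symptom relief as a goal, not as an expected rate, and gives no GCS distribution. With poor recovery or some worsening, the baseline share of variance falls and the loss can be small.
- **That chance imbalance in baseline GCS could produce a false positive.** Under randomization the unadjusted comparison is unbiased, and its standard error already reflects such imbalance. Stratification by severity limits part of it. Rejection with no true difference was about 5% or lower.
- **That the simulated powers measure the defect.** They depend on the model. The two models even disagree on whether the t test or Mann-Whitney does worse under good recovery. They support the direction and a plausible range, no more.

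Nor can GCS be called the only scored clinical measure: changes in symptoms are analysed by the same tests, which implies some score.

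**Conclusion.** The point holds as one of efficiency. An unadjusted test of GCS change discards the information in baseline GCS and the severity stratum, both already available. By the algebra, adjustment cannot lose precision in large samples, and ANCOVA was ahead of the t test on change in every scenario examined. The advantage is large if recovery is near the ceiling (about 9–22% against 22–67% in the 60% vs 80% case) and small if recovery is poor or some patients worsen (for example 7–18% against 10–28%). These figures rest on assumed GCS distributions and 76 to 89 patients per arm. The proportional-odds model offered below was not simulated.

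The planned test is neither biased nor prone to excess false positives. The primary overcorrection analysis and the sample size of 178 are untouched. The change is worth making, but the trial's main conclusion does not depend on it.

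**What to change.** In Statistical analyses, replace the two-sample test of GCS change with a model of GCS at 24 h, and likewise at 48 h, on treatment arm, baseline GCS and severity stratum. Use either ANCOVA with robust standard errors or, given the ceiling, proportional-odds regression, and name the choice before the data are compared by arm. Report raw mean change by arm descriptively. If change in symptoms is analysed as a score, treat it in the same way.

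The cost is a change of wording. No extra visits, measurements or patients are needed, and the named software, SPSS, can fit both models.

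### Change in symptoms is compared between arms without regard to entry severity, the randomization stratum, which makes the test conservative and costs power on a secondary outcome

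*Protocol article*

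**What the plan says.** Outcome measures lists "changes in symptoms between pretreatment and 24 and 48 h after treatment with 3% hypertonic saline" among the secondary outcomes and attaches no scale. Statistical analyses takes this item up together with GCS ("The differences in changes in symptoms and GCS scores between pretreatment and 24 and 48 h") and groups it with times to sodium targets and hospital stay ("and length of hospital stay will be analyzed using Student’s *t* test or the Mann-Whitney *U* test"). Neither section mentions adjustment for entry severity in this comparison.

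The text shown describes symptoms in two ordered classes. Study participants and measurements gives one list for each class, for example "Moderate symptoms include nausea, headache, drowsiness, general weakness, and malaise", and Table 1 repeats the two classes. A third state, relief, appears ungraded in the treatment goals ("to achieve symptom relief within the first 24 h") and in the rules for both arms. The only numeric score with stated assessment times is the GCS: "The GCS score will be assessed before treatment and at 24 and 48 h of treatment".

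The Randomization section uses the same two classes: "Randomization will be stratified based on the symptom severity related to hyponatremia". The Discussion mentions analysis within each severity level, but only for the interim analysis.

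**The concern.** With the classes given, a change score means subtracting one class from another. Coded 0 (relieved), 1 (moderately severe) and 2 (severe), a moderately severe patient who becomes symptom-free scores 1 and a severe patient who becomes symptom-free scores 2. Both have the same good result, yet their values differ because of where they started. Stratified randomization balances entry severity between the arms, so this spread cannot produce a spurious difference. An unstratified test still puts it into the standard error.

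At stake is the chance of detecting a real difference in symptom improvement, which is a treatment goal in both arms. A mean change in class also does not tell a reader how many patients were relieved.

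**Working it through.** **Inputs from the document.** Two-sided alpha 5%, power 80%, overcorrection 5% versus 20%, dropout 15%, 89 per arm (Sample size calculation); 1:1 allocation stratified by severity (Randomization).

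**Assumed, because the document does not give them.** Relief rates, share severe at entry, share of unrelieved severe patients who fall to moderate, and the 0/1/2 coding.

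**1. The plan's own figure.** Pooled two-proportion formula with mean rate 0.125: n = [1.96 × √(2 × 0.125 × 0.875) + 0.842 × √(0.05 × 0.95 + 0.20 × 0.80)]² / 0.15² = (0.917 + 0.383)² / 0.0225 ≈ 75.1, so 76 evaluable per arm. 75.1 / 0.85 = 88.4, which rounds up to the stated 89. The document states no power for symptom change.

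**2. Share of the change variance due to entry severity.** Let r be the relief rate in both classes, s the share severe, and f the share of unrelieved severe patients who fall to moderate.
- Moderately severe: mean r, variance r(1 − r).
- Severe: mean m = 2r + f(1 − r), variance 4r + f(1 − r) − m².
- Between-class variance: s(1 − s)(m − r)².

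Example with r = 0.70, s = 0.25, f = 0.5: m = 1.55; variances 0.210 and 0.5475; between 0.1875 × 0.85² = 0.1355; within 0.75 × 0.210 + 0.25 × 0.5475 = 0.2944. Share R² = 0.1355 / 0.4299 = 0.32.

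Over s = 0.10-0.50 and f = 0-0.8, R² is 4-39% at relief of 40-60%, 14-44% at 70%, 22-52% at 80%, 38-67% at 90% and 57-80% at 95%.

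**3. What this does to the test.** With severity balanced, the unstratified statistic is about √(1 − R²) times the stratified one, so the effective critical value is 1.96 / √(1 − R²).
- No true difference: R² = 0.368 gives 1.96 / 0.795 = 2.47, a rejection rate of about 1.4%. Simulation at that R² gave 1.5-1.6%.
- Power: a stratified test with 79% power has expected z = 1.96 + 0.81 = 2.77. At R² = 0.303 the effective critical value is 1.96 / 0.835 = 2.35, so power is Φ(0.42) ≈ 66%. Simulation gave 67% for Mann-Whitney and 63% for the t test.

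**4. Simulation at 89 per arm** (2,000 runs per setting; percentage of runs rejecting, with 10% / 25% / 50% severe at entry).

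| Relief assumed | t test on change | Mann-Whitney on change | Class adjusted for severity (ANCOVA) | Change, stratified rank test |
|---|---|---|---|---|
| 70% v 50% | 68.2 / 63.3 / 61.7 | 71.3 / 66.6 / 61.4 | 76.6 / 76.3 / 76.9 | 77.1 / 79.1 / 79.2 |
| Moderate 70% v 50%, severe 50% v 30% | 72.2 / 71.2 / 69.4 | 73.4 / 72.3 / 69.7 | 77.2 / 78.8 / 79.0 | 77.6 / 80.3 / 80.2 |
| 90% v 75% | 58.5 / 40.8 / 35.7 | 60.2 / 37.8 / 24.9 | 77.1 / 75.5 / 73.1 | 77.5 / 76.3 / 75.4 |
| 60% v 40%, no severe-to-moderate moves | 70.7 / 67.9 / 69.0 | 74.5 / 72.6 / 72.4 | 74.7 / 71.4 / 72.6 | 75.5 / 74.6 / 75.4 |
| 70% v 70% (no difference) | 2.8 / 1.5 / 1.7 | 3.3 / 1.6 / 1.3 | 4.8 / 4.6 / 5.2 | 4.7 / 4.8 / 4.8 |

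In the 60% v 40% row, adjustment gains nothing over Mann-Whitney beyond simulation error.

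**5. Simulation at 76 per arm, 30% severe, f = 0.5** (6,000 runs per setting). The tests are, in order: t test on change, Mann-Whitney on change, mean-score test on class stratified by severity, and stratified relief yes/no.
- Relief 80% / 60% (moderate / severe) v 60% / 40%: 61%, 63%, 67%, 75%.
- Relief 80% / 70% v 65% / 50%: 44%, 46%, 56%, 60%.
- No difference: 3.5%, 3.9%, 5.2%, 5.4%.

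**6. Is relief yes/no the better outcome?** Step 5 puts the whole treatment effect on complete relief. Suppose instead that the arms also differ in severe-to-moderate improvement (90% v 30% of unrelieved severe patients, assumed; 76 per arm).
- Relief 75% / 50% v 65% / 40%: planned Mann-Whitney 49-68%, stratified relief test 27%.
- Relief 70% / 50% v 60% / 30%: 62-87% against 36-43%.

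The ranking reverses. The stratified mean-score test on three classes kept an advantage of at least about 2 points over the planned tests here too.

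**The case against.** **The planned test is valid.** Mann-Whitney is standard for ordered data, and stratified randomization keeps the arms comparable. This stands. A reader might infer that the comparison is biased or prone to false positives; the rejection rates in step 4 show the opposite.

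**The coding is assumed.** The schedule figures and the full protocol are not shown, and the article gives no symptom scale. This stands as a limit. That symptoms are recorded only as classes is an inference from the text shown; a symptom count or score cannot be excluded, and the magnitudes above would not carry over to it. The absence of coding detail is not the point raised. The article does fix the test, and that test ignores the stratification factor.

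**Does the change mostly reflect entry severity?** A reader might infer so, but step 2 shows that more than half needs relief of about 80-90% or higher, which the document does not state. In the two step 5 scenarios the share is only 14-23%.

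**Stratification adds little to a relief yes/no test.** True: in the first step 5 scenario an unstratified chi-square test has 74-75% power against 74-76% stratified. The harm comes from subtracting the entry class and then ignoring it. In the 70% v 50% setting at 89 per arm, Mann-Whitney on the post-treatment class alone reaches 77-79%.

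**Replacing the outcome with yes/no relief is a trade-off.** This stands, by step 6. It discards a move out of the severe class, which includes seizure and coma.

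**Conclusion.** The point holds as a low-cost improvement to a secondary analysis. The stated test is unbiased but runs below its nominal level: about 2-4% at 76 per arm, and 1.3-3.3% at 89 per arm with 70% relief. Against a severity-adjusted analysis of the same classes it loses from about 2 points to more than 30, and most when relief is common. In the setting with 60% v 40% relief and no partial improvement, the loss against Mann-Whitney is nil to about 3 points, depending on the adjusted test.

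These sizes rest on the 0/1/2 grading and on assumed relief rates and severity mix. The documents do not support reading this as a threat to validity, nor as grounds for dropping the graded outcome in favour of yes/no relief. The primary outcome, the sample size and the interim rule are untouched.

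**What to change.** In Outcome measures, name the symptom outcome as the class (none, moderately severe, severe) at 24 h and at 48 h. If a symptom score exists in the full protocol, name that instead. In Statistical analyses, replace the unstratified comparison of symptom change with one stratified by or adjusted for entry severity: for example, a Cochran-Mantel-Haenszel mean-score test stratified by the randomization factor, or a proportional-odds model with entry severity as covariate. Report alongside it the proportion relieved per arm with a risk difference and 95% CI, as a supportive measure only.

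The cost is a sentence or two. Relief is already judged at the sample times, including 24 h and 48 h, to apply the treatment rules. The class of patients not yet relieved needs recording at those two times if it is not already, and any assessment of symptom change would need that anyway. No clinical procedure changes.
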